#### Rehabilitation

Hand Therapy intervention will be performed by Occupational Therapists who are experienced in treating distal radius fractures in hospital outpatient departments. Therapy will commence within 3 days of the operation. At this time the patients will have a thermoplastic static volar wrist orthosis fabricated and commence an early active mobilisation program as detailed in Table 1. Any deviation from the study protocol will be documented to control for in the analysis.

**Table 1 T1:** Rehabilitation protocol post-operation

**Time frame**	**Treatment guideline**
Day 1–2 post-op	**Advice and education**
	• Education regarding injury/fixation/and rehabilitation protocol- minimal axial loading
	• Non-loaded ADL’s with splint off

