### Trial interventions

The interventions being compared are:

Intervention A: Early surgical intervention using a Stainless Steel volar locking plate.

Intervention B: Early surgical intervention using a Titanium volar locking plate.

The hospital involved in the trial currently use both types of plate for open reduction and internal fixation of distal radius fractures and all of the surgeons involved are surgically experienced with volar plate fixation for distal radius fractures. The operative technique takes place under general anesthetic and each patient will undergo the surgery according to their random allocation of Intervention A or Intervention B. Randomisation will occur at the time of surgery booking after the patients has been appropriately consented and enrolled into the study.

All patients undergo general anaesthetic and high arm tourniquet control. The approach is via a volar incision and then through the bed of the flexor carpi radialis tendon. The plane between the flexor tendons and pronator quadratus is identified and pronator quadratus is then dissected carefully as a flap from the radial side to expose the underlying distal radius. Brachioradialis is released completely due to its adverse coronal plane deforming force upon the fracture.

Reduction of the fracture is dependent upon the fracture pattern and may be indirect with traction and manipulation, or direct with mobilization of the fragments directly with k-wires or bone punch. After the fracture has been initially temporarily stabilized with k-wires the volar multi-axial locking plate is applied and secured with screws to gain control of the radial and ulnar columns. It is paramount to ensure that the ulnar column is held securely to prevent any ulnar translocation. In the majority of cases the technique during surgery is to insert the variable angle distal row screws first according to the surgeons technique and to place them in the most appropriate subchondral configuration at the most appropriate depth whilst accommodating the variable fracture fragment configuration. The plate is reduced to the shaft and the diaphyseal screws are then inserted whilst fine-tuning fracture reduction [8]. If there is any significant bone loss the void is filled using calcium phosphate injectable bone substitute.

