	**Exercises**
	Commence active wrist ROM: dart throwing axis; wrist flexion/extension/pronation/supination/radial & ulnar deviation; finger tendon gliding; thumb extension, opposition
	• Commence active assist wrist extension/supination
	• AROM non-affected joints of upper extremity
Day 10	• Removal of sutures
	• Continue wrist orthosis
	• Commence scar management: massage, desensitization and application of silicone based products
	• Oedema Management as required: retrograde massage, compression, elevation
	• Continue exercise program
Weeks 2–3	• Continue wrist orthosis
	• Continue scar management
	• Ongoing oedema management as required
	• Light function in splint
	• Active assisted and passive wrist exercises
	• If significant difficulty achieving supination apply gentle tension rotational splint for Pronation/Supination. Commence dynamic rotational orthosis if required dependent on fracture healing, pain and oedema
	• Commence stretch with 500 g weight and heat.
Weeks 4–5	• Continue wrist orthosis for at risk activities only
	• Continue oedema and scar management as required.
	• Active, active-assisted, passive wrist extension/flexion/pronation/supination
	• Continue weighted stretches and dynamic orthotic use as required
Week 6	• Cease wrist orthosis
	• Commence grip and wrist strengthening (dependant on fracture healing)
	• Increase functional activity with affected hand
	• Dynamic orthotic to increase range of movement
	• Gradual increase in strengthening program
	• Wrist proprioception exercises
Week 8 weeks +	• Continue dynamic orthotic use as required
	• Continue active and passive wrist exercises
	• Ongoing strengthening program
	• Gradual increase with weight bearing, heavy lifting
	• Function/work hardening

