### Patient rated wrist evaluation (PRWE)

The PRWE is a 15-item questionnaire designed to measure wrist pain and disability in activities of daily living. The PRWE allows patients to rate their levels of wrist pain and disability from 0 to 10, (0 = no difficulty, 10 = unable to do) and consists of 2 subscales:

1) PAIN subscale – 5 items.

2) FUNCTION subscale - 10 items (specific and usual activities).

In addition to the individual subscale scores, a total score can be computed on a scale of 100 (0 = no disability), where pain and function problems are weighted equally.

The PRWE is a standardized outcome tool that is easy to administer and score, and complements traditional impairment and radiographic measures. The PRWE has been used to assess wrist-related pain and disability in various populations and its reliability, validity, and responsiveness have been tested and reported in published studies [17].

The secondary outcome measures in this trial are the:

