### Adverse events

The following adverse events will be recorded: significant reduction in movement (6 weeks or greater), high levels of reported pain (2 weeks or greater), significant reduction in function (6 weeks or greater), non-union, malunion, infection, chronic regional pain syndrome, implant failure (eg implant breakage, screw migration, loosening), fracture fixation failure (implant failing to maintain fracture fixation), tendon irritation (3 months or greater), tendon rupture, nerve injury, excessive scarring or hypersensitivity (6 weeks or greater).

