#### Statistical analysis

Baseline demographic and clinical data will be reported using descriptive statistics and tabulated (e.g. Students *t*-test for continuous variables and Pearson chi-square for categorical variables). Between group differences in baseline data will be examined using unpaired conventional tests of hypothesis (such as unpaired t-tests) depending on the nature of the data. Between group and within group differences in outcome measures over time will be examined using a priori unpaired and paired conventional tests of hypothesis (such as Analysis of Variance with simple effects examined using t-tests) depending on the nature of the data. Bonferroni adjustments for multiple comparisons will be made where appropriate to mitigate risk of type-1 error. The complication rates will be reported in terms of frequency. The frequencies of complications will be compared using statistical analysis such as the Pearson chi-square statistic. For missing data values at different time points, a mixed linear regression model for repeated measures will be performed. Subanalysis for age will be undertaken to account for patients with osteoperotic bone.

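### The commitment to control for any protocol deviation is not limited to a sensitivity analysis and, if applied to the primary comparison, can bias the effect of the allocated plate

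*Protocol article*

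**What the plan says.** The commitment is in the Rehabilitation section of the protocol article: "Any deviation from the study protocol will be documented to control for in the analysis". It covers every deviation. It names no method and does not say which analysis it applies to.

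Three other parts of the article bear on it:

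- **Timing.** Under Trial interventions: "Randomisation will occur at the time of surgery booking after the patients has been appropriately consented and enrolled into the study". Under Rehabilitation: "Therapy will commence within 3 days of the operation". A rehabilitation deviation therefore comes after both allocation and implantation.
- **Rehabilitation content.** Table 1 makes some steps conditional on the patient's state, for example "Commence dynamic rotational orthosis if required dependent on fracture healing, pain and oedema" and "Commence grip and wrist strengthening (dependant on fracture healing" (strengthening, at week 6). Other steps are tied to a date only, such as starting active wrist movement on day 1–2 and stopping the wrist orthosis at week 6.
- **Analysis.** The Statistical analysis section says "Between group and within group differences in outcome measures over time will be examined using a priori unpaired and paired conventional tests of hypothesis", giving analysis of variance and t-tests as examples. It adds chi-square tests for complications and a mixed model for missing values. No deviation covariate is named, and nothing says that the primary comparison is by randomised group without such an adjustment.

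The Outcome measures section does keep all patients in the analysis, but in the context of other injuries that may affect outcome, not of protocol deviations.

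**The concern.** The trial asks whether patients fare the same with either plate. Randomisation answers that for the total effect of being allocated one plate or the other. A deviation recorded after surgery is not a baseline characteristic. If it is partly a result of the plate, adjusting for it does two things:

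- It removes the part of the plate effect that runs through the deviation. A plate that leaves more patients sore and slow to mobilise would be credited as if they had mobilised on time.
- It compares deviators with deviators and non-deviators with non-deviators. If an unmeasured prognostic factor drives both deviation and PRWE, those groups are no longer balanced between arms, and a difference can appear where none exists.

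A further hazard is that the article does not define which departures count. The covariate could be settled after the data are seen.

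**Working it through.** **1. Is a path from plate to deviation plausible on the article's own text?**

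The Background says that plate and screw type contribute to complication rates. Table 1 ties progression to healing, pain and oedema. The same factors could cause departures from the date-only steps. The primary outcome overlaps with them: "The PRWE is a 15-item questionnaire designed to measure wrist pain and disability in activities of daily living". So the path is plausible, but the article gives no deviation rate and does not say that deviations differ by plate.

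**2. When does adjustment bias the estimate?**

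This was checked by simulation with 1,000,000 patients per scenario. All inputs are assumed. The deviation rate is 20% in one arm. The plate effect on PRWE is estimated by a linear model with and without a yes/no deviation covariate. Where an unmeasured factor is present, it shifts both the chance of deviating and PRWE (5 points per SD).

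| Deviations by arm | Points per deviation | Direct plate effect | Unmeasured factor | Unadjusted (total) effect | Adjusted effect |
|---|---|---|---|---|---|
| 20% v 20% | 10 | 0 | no | about 0 | about 0 |
| 20% v 20% | 10 | 0 | yes | about −0.1 | about −0.1 |
| 20% v 30% | 10 | 0 | no | 0.9 | about 0 |
| 20% v 40% | 10 | 0 | no | 2.0 | about 0 |
| 20% v 50% | 10 | 0 | no | 3.0 | about 0 |
| 20% v 40% | 0 | 0 | yes | about 0 | −1.0 |
| 20% v 40% | 10 | 5 | yes | 7.0 | 4.1 |

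In the first two rows deviations are equal by plate and adjustment does no harm. In the others the adjusted figure is not the total effect.

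**3. Size at the trial's planning values.**

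From the Sample size section: 65 per group, 30% loss, difference 10, SD 15. Alpha is not stated, so two-sided 0.05 is assumed.

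- Evaluable per group: 65 × 0.70 = 45.5.
- Standard error: 15 × √(2/45.5) = 3.14.
- Power for 10 points (noncentral t): 88.2%. The article states 95%. That gap is a separate matter and does not affect this point.

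With no unmeasured factor, adjusted effect = total effect − (excess deviation proportion × penalty). Assuming a 20-point excess and a 15-point penalty: 10 − 0.20 × 15 = 7 points.

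*SD kept at 15:* power for 7 points is 59.6%.

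*Variance removed by the covariate counted:* with total within-arm SD 15, residual variance = 225 × (1 − w), where w is the mean over arms of p(1 − p). Because arm and deviation are correlated, the variance of the plate estimate is multiplied by 1/(1 − r²), with r² = 0.20² × 0.25 / [p̄(1 − p̄)]. For 20% v 40%:

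- w = (0.16 + 0.24)/2 = 0.20, so residual variance is 180 and residual SD 13.42.
- r² = 0.01/0.21 = 0.048, so the factor is 1.05.
- Standard error = 13.42 × √(1.05 × 2/45.5) = 2.88, and power is 67%.

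The same steps give 61% at 5% v 25%, 64% at 10% v 30% and 69% at 30% v 50%.

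**4. Range over smaller assumptions** (SD kept at 15, true difference 10). Each cell gives points removed, then power.

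| Excess deviations | 5-point penalty | 10-point penalty | 15-point penalty |
|---|---|---|---|
| 0 | 0; 88% | 0; 88% | 0; 88% |
| 5 points | 0.25; 87% | 0.5; 85% | 0.75; 83% |
| 10 points | 0.5; 85% | 1.0; 81% | 1.5; 76% |
| 20 points | 1.0; 81% | 2.0; 71% | 3.0; 60% |

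**The case against.** The strongest reply is that this is one loose phrase in a rehabilitation section. The Statistical analysis section does not carry it into any named test, and t-tests and chi-square tests take no covariate. The phrase could equally mean a stratified or sensitivity analysis, and details of handling deviations usually belong in a statistical analysis plan. This stands in part: the article does not fix a biased primary analysis. But it is a stated intention, not silence. It covers all deviations, and nothing in the article keeps it out of the primary comparison.

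A reader might infer more: that deviations are a consequence of the plate, so the plan will bias the result. The article does not support that. Missed therapy, scheduling and patient choice also produce deviations, and these need not differ by plate. Two pieces of apparent support fail:

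- Holding back strengthening because healing is doubtful is allowed by Table 1, so it is not a deviation.
- The Adverse events list ("fracture fixation failure (implant failing to maintain fracture fixation), tendon irritation (3 months or greater), tendon rupture, nerve injury") links none of its items to a rehabilitation departure. Tendon irritation counts only from 3 months, after the dated steps of Table 1.

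The illustration also rests on an excess and a penalty that the article does not give. A single power figure of about 60% would be the pessimistic end, because adjustment also removes residual variance.

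**Conclusion.** The point holds as a matter of badly fixed wording. The article announces control for deviations that arise after randomisation, does not limit this to a sensitivity analysis, and leaves it unreconciled with the named tests. If applied to the primary comparison, the adjustment can bias the effect of the allocated plate, provided that deviations depend on the plate or its early results. If they do not, it causes no bias.

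Direction and size cannot be known from the document. With assumed excesses of 0 to 20 percentage points and penalties of 5 to 15 points, the part removed runs from 0 to 3 points of a 10-point difference. At the top of that range power falls from 88% to about 60–69%, depending on the baseline deviation rate and whether the reduced residual variance is counted. These power figures assume two-sided 0.05, 45.5 per group and no unmeasured common cause of deviation and outcome. The conclusion that the wording needs changing does not depend on them.

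**What to change.** Replace the sentence in the Rehabilitation section with:

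> *Deviations will be documented and summarised by arm; the primary analysis will be by randomised group and will not adjust for post-randomisation deviations; any deviation-based analysis will be a labelled sensitivity analysis.*

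The Statistical analysis section should carry the same rule so that the two agree. If a sensitivity analysis is wanted, the deviations that count should be defined before the data are seen.

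The cost is one sentence and a matching line. Data collection, sample size and rehabilitation content stay as they are.

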	**Wound**
	**•** Remove post-operative dressing. Redress with simple dressing
	**Oedema**
	• Elevation and retrograde massage for oedema.
	• Application of compression to manage oedema as required
	**Orthosis**
	• Fabrication of thermoplastic static volar wrist orthosis in extension ( ≥15 degrees), ensuring full digit flexion achievable
	**Exercises**
	Commence active wrist ROM: dart throwing axis; wrist flexion/extension/pronation/supination/radial & ulnar deviation; finger tendon gliding; thumb extension, opposition
	• Commence active assist wrist extension/supination
	• AROM non-affected joints of upper extremity
Day 10	• Removal of sutures
	• Continue wrist orthosis
	• Commence scar management: massage, desensitization and application of silicone based products
	• Oedema Management as required: retrograde massage, compression, elevation
	• Continue exercise program
Weeks 2–3	• Continue wrist orthosis
	• Continue scar management
	• Ongoing oedema management as required
	• Light function in splint
	• Active assisted and passive wrist exercises
	• If significant difficulty achieving supination apply gentle tension rotational splint for Pronation/Supination. Commence dynamic rotational orthosis if required dependent on fracture healing, pain and oedema
	• Commence stretch with 500 g weight and heat.
Weeks 4–5	• Continue wrist orthosis for at risk activities only
	• Continue oedema and scar management as required.
	• Active, active-assisted, passive wrist extension/flexion/pronation/supination
	• Continue weighted stretches and dynamic orthotic use as required
Week 6	• Cease wrist orthosis
	• Commence grip and wrist strengthening (dependant on fracture healing)
	• Increase functional activity with affected hand
	• Dynamic orthotic to increase range of movement
	• Gradual increase in strengthening program
	• Wrist proprioception exercises
Week 8 weeks +	• Continue dynamic orthotic use as required
	• Continue active and passive wrist exercises
	• Ongoing strengthening program
	• Gradual increase with weight bearing, heavy lifting
	• Function/work hardening

#### Radiological assessment

Normal radiological assessment of the wrist using either x-ray or computed tomography scans will be performed. Diagnosis will be confirmed with x-ray or computed tomography scan. X-rays will be routinely taken post-operatively at 2 weeks, 6 weeks and thereafter to assess bony fracture union and any fracture or hardware related complications as required. An X-ray will also be taken at final follow-up at two years to assess for any bony or hardware related complications. Radiographic assessments will not be blinded.

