## Methods/Design

### Design

This is a prospective double blind randomized clinical trial. This study was approved by the Metro South Human Research Ethics Committee (Ref: HREC/12/QPAH/293) and registered with the Australian New Zealand Clinical Trials Registry (ANZCTR) (Ref: ACTRN12612000969864).

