### Radiographic evaluation

Standard posterior-anterior, lateral and oblique radiograph projection views will be taken to confirm diagnosis pre-operatively. X-rays will then be routinely performed as per the standard level of care to assess for union, standard radiographic parameters and hardware complications. An additional x-ray will also be taken at 24 months post-operation to assess for malunion, radiographic parameters and hardware complications.

These outcomes will be administered by a blinded assessor at the timeframes detailed in Table 3:

**Table 3 T3:** Intervals for outcome measures

**Assessment**	**Baseline**	**2 weeks**	**6 weeks**	**3 months**	**6 months**	**1 year**	**2 years**
**PRWE**			X	X	X	X	X
**Patient satisfaction**			X	X	X	X	X
**Pain**		X	X	X	X	X	X
**Radiological outcomes**	X	X	X	*	*	*	X
**AROM**		X	X	X	X	X	X
**Complications**		X	X	X	X	X	X
**EQ5D**	X		X	X	X	X	X
**Quick DASH**			X	X	X	X	X
**Grip strength**				X	X	X	X

*Only if required as part of treatment/normal care.

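### The double-blind label and the blinded-assessor statement do not hold for the radiological outcomes and film-based complications, because radiographs are read unblinded

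*Protocol article*

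**What the plan says.** Three statements in the protocol article bear on blinding.

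- Design: "This is a prospective double blind randomized clinical trial". The blinded roles are not named.
- Radiological assessment: "Radiographic assessments will not be blinded".
- Radiographic evaluation, directly after the X-ray paragraph and closing the list of outcome measures: "These outcomes will be administered by a blinded assessor at the timeframes detailed in Table 3".

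Table 3 has a row for "Radiological outcomes" and a row for complications. Its only footnote concerns films taken when normal care requires them; it exempts nothing from blinding.

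X-rays are the stated means of judging several complications. The routine post-operative films are taken "to assess bony fracture union and any fracture or hardware related complications as required", and the 24-month film is taken "to assess for malunion, radiographic parameters and hardware complications". The Adverse events section lists, among others, "non-union, malunion, infection, chronic regional pain syndrome, implant failure (eg implant breakage, screw migration, loosening), fracture fixation failure". The Statistical analysis section then compares complication frequencies between the groups.

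**The concern.** A reader of the Design section and Table 3 would conclude that every tabulated outcome is assessed by someone who does not know the allocation. For anything read from a film, the Radiological assessment section says otherwise. The randomised factor is the plate itself, and the plate is in the film.

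What is at stake is how far the between-plate comparison of radiological results and film-based complications can be trusted, and how it will be described when reported. The Abstract names radiological outcomes and complication rates among the things the trial will compare. Table 2 records both on study-specific checklists. Calls such as malunion or loosening involve judgement, and a reader who knows the plate may make them differently in the two arms. If the report carries over the double-blind label unqualified, it credits these comparisons with a protection that the plan itself says they lack.

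**Working it through.** The plan gives no figure on this point, so the check is a comparison of texts and two counts.

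**1. What the blinded-assessor sentence covers.** It refers to the outcomes at the Table 3 times. The rows of Table 3 are: PRWE, patient satisfaction, pain, radiological outcomes, active range of movement, complications, EQ-5D, QuickDASH, grip strength. That is 9 rows. Two of them (radiological outcomes, complications) rest wholly or partly on films. Neither is exempted.

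**2. What the unblinded statement covers.** It covers radiographic assessments, without restriction by visit or purpose. By Table 3, films are scheduled at baseline, 2 weeks, 6 weeks and 2 years, and at 3 months, 6 months and 1 year only if care requires them.

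**3. Overlap.** The radiological outcomes row falls under both statements in full. The complications row falls under both as far as a complication is judged from a film.

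**4. Which complications those are.** The Adverse events section lists 13 categories:

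| Basis | Categories | Count |
|---|---|---|
| Mainly films | non-union; malunion; implant failure; fracture fixation failure | 4 |
| Clinical or patient-reported | reduced movement; high pain; reduced function; infection; chronic regional pain syndrome; tendon irritation; tendon rupture; nerve injury; scarring or hypersensitivity | 9 |

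4 + 9 = 13. Placing the four under films follows the purposes given for the X-rays: union, malunion, and fracture or hardware complications.

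**5. Position of these outcomes.** The primary outcome is the PRWE, a patient-rated questionnaire, and the Abstract sets the primary aim at six months. Adverse events and radiographic evaluation stand in the list of secondary outcomes.

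**6. Result.** Taken as written, the two sentences conflict for one full row of Table 3 and for 4 of the 13 categories behind another. The label in the Design section carries no qualification that would settle which governs.

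**The case against.** The best reply is that the specific statement qualifies the general one. Questionnaires, goniometry and grip tests are administered, whereas films are taken and read. On that reading the blinded assessor was never meant to cover radiographs, and the article discloses the unblinded reading openly. This has force: nothing is hidden, and the fault is a missing exception. It does not remove the point, because the blinded-assessor sentence follows the radiographic paragraph directly and refers to a table that includes radiological outcomes and complications. The reader has to supply the exception.

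Unblinded film reading can also be a legitimate, disclosed choice, and a condensed article may leave visit procedures to the full protocol. Both are accepted. The point is the mismatch between published statements, not missing detail.

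Four stronger readings are tempting, and the article does not support them.

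- *The primary assessment is compromised.* A reader might infer this if the same assessor also reads the films. The article does not say who reads them. The 6-month film is taken only if care requires it, and the PRWE is rated by the patient. If one person did both tasks, films at 2 and 6 weeks could reveal the plate before the 6-month visit. That is a possible carry-over risk only.
- *The bias can be sized from the 8% complication rate in the Background.* That rate comes from a retrospective series and covers complications of all kinds, such as chronic pain and tendon tears. It is not a rate of film-based events, and the trial's own list differs from it.
- *These are primary comparisons.* They are named for comparison in the Abstract but stand as secondary outcomes.
- *Double blind means that patients are blinded.* The article never says so.

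**Conclusion.** The point holds as an inconsistency about a design safeguard. The stated blinding does not apply to the radiological outcomes or to the film-based complications: 2 of 9 Table 3 rows are touched, the second only for 4 of its 13 event categories. All are secondary outcomes. The remaining nine event categories need not depend on films.

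The conclusion rests on two readings: that the blinded-assessor sentence covers every row of Table 3, as its wording does, and that the four events named are judged mainly from films. The size of any bias cannot be computed. The article gives no rate of film-based events, does not say who reads the films, and does not say whether the two plates can be told apart on a radiograph. Nothing in it shows an effect on the PRWE. The correction is worth making because it concerns outcomes that the trial sets out to compare and costs very little.

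**What to change.** 1. **Design.** Name the blinded roles in place of the bare label, and state that radiograph readers are not blinded. The sponsor should confirm whether patients are blinded before any wording says so.
2. **Radiographic evaluation, sentence introducing Table 3.** Exempt radiological outcomes and film-based complications (non-union, malunion, implant failure, fixation failure) from the blinded-assessor statement. A footnote to the two rows would do.
3. **Separation of roles.** Require that the blinded clinical assessor does not read films and completes PRWE, VAS, QuickDASH, EQ-5D, movement and grip without access to films or operation notes. This closes the possible carry-over route.
4. **Reporting.** Label comparisons of radiological outcomes and film-based complications as unblinded.

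The cost is a change of wording and a rule on access at visits, with no added patients and no independent film reader. The drawback is a less favourable blinding label. These changes make the description accurate and protect the clinical measures; they do not remove any bias in the film readings themselves.
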